### 2.6. Intervention

The experimental group will participate in a 12-week home-based programme. This programme will include patient education on the benefits of physical exercise and guidance on how to perform it safely with a colostomy, resistance training targeting major muscle groups, core-strengthening exercises, and aerobic walking exercise. The Template for Intervention Description and Replication (TLDieR) checklist [35] will be followed. The control group will receive standard medical care along with an informational leaflet on colostomy management and the main barriers to physical activity they may encounter.

#### 2.6.1. Experimental Group

Participants assigned to the intervention group will undergo a 12-week home-based graded exercise programme, structured as follows:Initial Session

The initial session will be conducted individually to inform the patient about the benefits of exercise and how to perform it safely with a colostomy. Questions will be addressed, and the structure of the intervention and data collection will be explained.

Week 1–4: Introduction and Supervised Sessions

Participants will complete one 15 min weekly supervised online session, including warm-up, resistance training, core training (based on Rune et al., 2020 recommendations) [36] and cool-down. Resistance exercise training will target major muscle groups involved in daily activities, including lunges, leg lifts, bridges, side bridges, upper limb raises, sit-to-stand and step-ups. Participants will also perform a second weekly self-paced walking session, starting at five minutes, progressively increasing by five minutes per week to a target of 45–60 min.

Week 5–8: Progressive Training

Participants will complete one supervised session, one additional session repeating the same exercises with physiotherapist support if needed and one walking session.

Week 9–12: Consolidation and Independent Sessions

Participants will perform two core and resistance exercise sessions and two walking sessions weekly.

Participants will record perceived exertion, pain, and discomfort after each session in a training diary, which will be reviewed weekly by the physiotherapist. Exercise intensity will be individually adjusted and monitored using the Borg Rating of Perceived Exertion (RPE) scale, targeting a moderate intensity level (12–14 on the 6–20 scale). The use of the RPE scale ensures that exercise load is safely tailored to each participant’s tolerance, minimizing the risk of adverse effects.

Supervised sessions will be conducted via a secure video-conferencing platform (Google Meet^®^), ensuring real-time interaction between the physiotherapist and the patient. Each session will include live demonstrations, performance feedback, and clarification of patient questions. Adherence and technical feasibility will be recorded.

Participants will receive both written and verbal instructions on how to access and use the Google Meet^®^ platform prior to the first supervised session. A brief test connection will be performed to ensure appropriate technical setup. All participants will maintain an exercise diary, available in both paper and digital format, to record session completion, perceived exertion, and any discomfort or adverse events. The physiotherapist will review these logs weekly via telematic communication and provide individualized feedback and motivational reinforcement. Additionally, participants will be able to contact the research team via an institutional email address for technical assistance or clarification during the intervention period. All telematic interactions will be conducted in compliance with institutional data protection and confidentiality policies.

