## Abstract

**Background/Objectives:** Permanent colostomy requires significant physical and psychological adaptation. Patients often experience reduced physical activity, impaired quality of life, and fear of movement. Current exercise recommendations are inconsistent, and no consensus exists on safe return to activity. This study aims to evaluate the effect of a 12-week home-based graded exercise programme on physical activity, quality of life, kinesiophobia, exercise capacity, and self-efficacy in patients with permanent colostomies. **Methods:** This randomized controlled trial will recruit 51 adults with permanent colostomies, beginning six weeks post-surgery. Participants will be randomized (1:1) to an intervention or control group. The intervention group will receive a 12-week home-based exercise programme including patient education, resistance and core training, and progressive aerobic walking. The control group will receive standard medical care and an informational leaflet. Primary outcomes include physical activity (steps/day), quality of life (Stoma-QoL), kinesiophobia (Tampa Scale), exercise capacity (6-Minute Walk Test), and self-efficacy (General Self-Efficacy Questionnaire). Follow-up will be conducted at baseline, post-intervention, and six months. Data will be analyzed using intention-to-treat principles with a significance threshold of *p* < 0.05. **Conclusions:** This trial will be the first to assess the effects of a structured, home-based graded exercise programme in individuals with permanent colostomies. The findings are expected to provide evidence on the efficacy of exercise for improving physical and psychological outcomes in this population and to inform clinical guidelines for safe, individualized activity resumption.

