## 1. Introduction

A colostomy is a surgical procedure performed to divert intestinal transit when anatomical or functional abnormalities prevent normal fecal evacuation through the anal canal. It creates an opening in the abdominal wall through which waste is expelled into an external pouch [1,2].

Colostomies represent a primary therapeutic option for conditions such as colorectal cancer, diverticulitis, severe trauma, inflammatory bowel diseases, and congenital disorders. Depending on the underlying cause, colostomies may be temporary or permanent. Permanent colostomies, in particular, require substantial adaptation, as they affect gastrointestinal function, body image and daily activities [3].

In the United States, it is estimated that nearly one million individuals currently live with an ostomy, with 100,000 to 130,000 new procedures performed each year [4]. Across the European Union, it is estimated that 725,000 to 1 million individuals live with an ostomy, a figure expected to rise in parallel with the increasing prevalence of inflammatory bowel disease and other gastrointestinal disorders [5]. This condition may lead to complications that adversely affect quality of life, often resulting in physical, psychological and social challenges [4,6,7,8,9,10].

Stoma-related issues, such as bleeding, necrosis, prolapse and hernias, are common and frequently accompanied by sexual dysfunction, fatigue and bowel irregularities [1,11,12,13]. These impairments are closely linked to psychological distress, including depression, anxiety [14], disturbances in body image [15] and decreased physical activity [16,17].

Russell et al. investigated the attitudes and perceptions of 2631 ostomy patients regarding exercise, reporting a prevalent fear of physical activity, low activity levels, limited knowledge, and the perception of parastomal hernia risk as a major barrier to participation in exercise programmes [17]. Interventions in this population have primarily targeted hernia prevention [18], improvements in quality of life [19,20,21,22,23], pain reduction, and mental health support [22,24,25]. However, there is currently no consensus regarding the safe resumption of physical activity following colostomy, highlighting the need for gradual, individualized exercise programmes that educate patients and promote safe and progressive activity.

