#### 2.6.2. Control Group

The control group will receive standard medical care and an informational leaflet covering colostomy management and common barriers to physical activity. No supervised exercise intervention will be provided.

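### Adverse events are described as recorded only in the exercise diary of the experimental arm and no safety outcome is listed, so any statement about safe resumption of activity would have no comparator

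*Protocol article*

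**What the plan says.** Section 2.6.1 (Experimental Group) describes the diary twice. The first time it is tied to exercise sessions: "Participants will record perceived exertion, pain, and discomfort after each session in a training diary". The second time, after the instructions for joining the video sessions, the article assigns it to all participants, on paper or digitally, and gives its purpose as "to record session completion, perceived exertion, and any discomfort or adverse events". It continues: "The physiotherapist will review these logs weekly via telematic communication and provide individualized feedback and motivational reinforcement".

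Section 2.6.2 (Control Group) reads: "The control group will receive standard medical care and an informational leaflet covering colostomy management and common barriers to physical activity". It adds: "No supervised exercise intervention will be provided". It mentions no diary, scheduled contact or event recording.

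Section 2.7 lists five primary outcomes, together with adherence (by diary), satisfaction and feasibility. The feasibility items go down to technical faults and digital literacy. No adverse-event or stoma-complication outcome is listed. Section 2.9 contains no harms summary, and none of the three tables planned in Section 3 is described as covering harms.

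The Introduction describes stoma problems, hernia among them, as common, and reports from a survey "the perception of parastomal hernia risk as a major barrier to participation in exercise programmes". The Abstract expects the findings "to inform clinical guidelines for safe, individualized activity resumption". The Discussion credits telehealth delivery with picking up complications early.

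**The concern.** Part of the trial's rationale is that there is no agreed way to return to activity safely after a colostomy. A reader will therefore look in the results for evidence on harm.

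Followed as written, the plan yields a list of events from exercising patients, collected weekly for 12 weeks, with nothing gathered in the same way from controls. That list is hard to interpret. Where stoma problems are common without exercise, a count from one arm cannot separate events due to the programme from events that would have happened anyway.

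If control events noticed by chance were later used as a comparator, the arm questioned every week would tend to show more events even with equal true risk. That distortion runs against exercise. In addition, the diary belongs to the 12-week programme, so no event recording is described in either arm between its end and the six-month assessment.

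**Working it through.** **Step 1. Which arm keeps the diary?** The article does not settle this in words, so the indications are set side by side.

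- For both arms: the subject of the sentence is all participants.
- For the exercise arm only: the sentence stands under the Experimental Group heading; it follows the instructions for the supervised video sessions; the diary logs session completion and exertion; the review is paired with feedback and motivation, which is programme delivery; Section 2.6.1 uses the unqualified word for participants to mean the intervention arm throughout; and Section 2.6.2 lists what controls receive without mentioning a diary.

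The exercise-arm reading is a strong inference, not an explicit statement.

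**Step 2. Harms content by section.**

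| Place | Exercise arm | Control arm |
|---|---|---|
| 2.6.1 / 2.6.2 | Diary with adverse events, reviewed weekly | None described |
| 2.7 Outcomes | No safety outcome | No safety outcome |
| 2.9 Analysis | No harms summary | No harms summary |
| 3 Planned tables | No harms content described | No harms content described |

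Intensity of ascertainment: 12 weeks × 1 review per week = up to 12 reviews in the exercise arm, against 0 described in controls.

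**Step 3. How much could safety data of this size show?** The plan gives no safety figure to reproduce. Inputs from Section 2.8 and the 1:1 allocation: 44 evaluable patients, so 44 / 2 = 22 per arm; 51 randomised, so 25 or 26 per arm.

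If no event is seen in n patients, the one-sided 95% upper bound on the true risk is 1 − 0.05^(1/n):

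- n = 22: 1 − 0.05^(1/22) = 12.7%
- n = 25: 1 − 0.05^(1/25) = 11.3%
- n = 26: 1 − 0.05^(1/26) = 10.9%

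**Step 4. Would collection in both arms give a test?** The article states no event rates, so these are assumptions chosen to span a range. With 25 per arm and a two-sided 5% level:

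| Assumed risks | Power |
|---|---|
| 5% vs 15% | 21% |
| 10% vs 20% | 16% |
| 10% vs 30% | 42% |

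Equal collection in both arms removes the ascertainment bias but leaves the data descriptive.

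**The case against.** The case on the other side has five parts.

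1. *Safety is not the trial's aim.* This stands. The aim and hypothesis in the Introduction name five efficacy outcomes, none of which depends on adverse-event capture. A reader might infer that the trial cannot meet its stated aim. The documents do not support that: safe resumption is an expected contribution in the Abstract, and Section 5 (Conclusions) makes no safety claim.

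2. *Hernia is not presented as the main hazard of exercise.* This also stands. The Introduction reports patients' perception of hernia risk as a major barrier, which concerns fear, and the trial does measure fear of movement.

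3. *The article never says that control events go unrecorded.* This is correct. Controls receive standard care and attend the planned assessments, and the diary wording covers all participants. A reader might infer that nothing is collected in controls; the text supports only that nothing is described. If controls are meant to keep the diary, Section 2.6.2 should say so, and a log of sessions and exertion would be a poor instrument for them.

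4. *A journal article leaves adverse-event procedures to the full protocol.* This is partly right, and definitions and reporting routes are not criticised here. But the article is not silent: it states a method of capture and places it in one arm, while itemising much smaller outcomes.

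5. *No comparison of harms is planned, so none can be biased.* This is true of Section 2.9. The bias is conditional on someone making the comparison. Without one, the remaining problem is a one-arm count with no background rate.

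**Conclusion.** The point holds as a limited design weakness that should be corrected before recruitment. As described, adverse-event capture is one-sided, with up to 12 weekly reviews against none, and no safety outcome or by-arm summary is listed. The efficacy results are untouched. The Abstract's wording on safe resumption would rest on uncontrolled data from 22 to 26 exercised patients, where even zero events is compatible with a true risk of about 11% to 13% at the one-sided 95% bound.

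It would go too far to say that the trial can yield no safety information. The diary gives some description of events in the exercise arm; what is missing is a comparator.

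The conclusion assumes that the diary belongs to the exercise arm, as its section and content indicate, and that the full protocol, which is not shown, does not already provide for equal collection. If it does, the remaining correction is to say so in the article.

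**What to change.** - **Section 2.7:** add a descriptive safety outcome covering stoma complications and any adverse event needing medical contact. Record it on the same checklist in both arms, from participant report and existing records, by the blinded assessor at the post-intervention and six-month assessments already planned.
- **Section 2.9 and the planned tables:** tabulate these events by randomised arm with exact confidence intervals and no significance test. Report diary events separately, labelled as intervention-only.
- **Section 2.6:** state which arm keeps the diary.
- **Abstract:** describe the safety evidence as preliminary.

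The cost is a few minutes per assessment, with no added visit. Because the checklist uses report and records, it does not ask the assessing physiotherapist to diagnose stoma complications. Two limits remain: participants know their allocation, which may colour what they report, and the data will be descriptive only. The Data Availability statement says that no data have yet been collected, so the change can still be made; control-arm events not recorded prospectively would be hard to recover later.

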#### 2.6.2. Control Group

The control group will receive standard medical care and an informational leaflet covering colostomy management and common barriers to physical activity. No supervised exercise intervention will be provided.

### 2.7. Outcomes

Patients will be contacted during follow-up visits conducted by the nursing service. Patients will be informed of the study, and if they agree to participate, a face-to-face appointment will be arranged. The initial evaluation will be performed once informed consent has been obtained. Data collection will include anthropometric variables (age, educational level, weight, height, marital status, employment status, and educational background), comorbidities assessed using the Charlson Comorbidity Index [37] and relevant clinical history data (medical history, indication for surgery, and regular medication). Participants’ perception of exercise will be measured using the Exercise Benefits/Barriers Scale [38].

#### 2.7.1. Primary Outcomes

Physical activity levels will be assessed via daily steps and energy expenditure, measured using a uniaxial accelerometer-based pedometer [39]. Participants will receive verbal and written instructions on its use. The device will be positioned at the left anterior superior iliac spine using a belt. Participants will be instructed to wear the pedometer throughout the day, except during sleep or bathing. For analysis, the mean values from the last seven consecutive days will be used. This device has demonstrated adequate reliability and validity in clinical and older populations [40,41]. The uniaxial accelerometer selected for this research has demonstrated adequate validity and reliability for step counting and energy expenditure estimation in clinical and older populations. Its simplicity and ease of use are advantageous for promoting adherence and minimizing technical difficulties in a home-based setting.

Quality of life will be assessed using the Stoma Quality of Life Questionnaire (Stoma-QoL). This disease-specific instrument has demonstrated strong reliability and validity, with good internal consistency and construct validity, and was developed to assess the physical, psychological, and social impact of living with a temporary or permanent stoma [42]. The questionnaire consists of 20 items covering domains such as social and leisure limitations, body image, physical activity, emotional wellbeing and stoma care. Each item is rated on a 4-point Likert scale ranging from “never” to “always”. Scores are transformed to a 0–100 scale, with higher values indicating better perceived quality of life. The Stoma-QoL has been validated in multiple languages, including Spanish, and demonstrates adequate reliability, making it suitable for both clinical and research settings [43,44].

Kinesiophobia is defined as an excessive, irrational and debilitating fear of movement, based on the perceived vulnerability to pain or reinjury [45]. It will be assessed using the 11-item version of the Tampa Scale of Kinesiophobia (TSK), a self-administered questionnaire widely employed to evaluate fear of movement or injury across diverse clinical populations. Each statement is rated on a 4-point Likert scale (1–4), yielding a total score ranging from 11 to 44, with higher scores indicating a greater level of kinesiophobia. The TSK has demonstrated strong reliability and validity, and a Spanish version is available. It shows adequate internal consistency and test–retest reliability, with a Cronbach’s alpha coefficient of 0.79 [46,47].

The Six Minute Walk Test (6MWT) is a functional test used to assess submaximal aerobic capacity and an individual’s functional status [48]. It is a simple, easy-to-administer test that measures the distance a person can walk along a flat, straight 30 m course over a period of six minutes. Heart rate, oxygen saturation, dyspnoea, and lower limb fatigue are monitored before and after the test. The 6MWT has demonstrated excellent reliability and validity and is widely used for the assessment and monitoring of chronic conditions [49], including cardiovascular and respiratory diseases, musculoskeletal conditions [50], cancer [31], and neurological disorders [51].

Self-efficacy is defined as the perceived capability to perform specific actions required to achieve concrete goals. In individuals with chronic disease, self-efficacy is defined as the patient’s perception of their ability to manage various aspects of their illness and its treatment [52]. It will be assessed using the 4-item General Self-Efficacy Questionnaire. Each item is rated on a scale from 1 to 10, where 0 indicates a lack of confidence in managing the indicated actions, and 10 represents complete confidence in handling the specified situation. Higher scores reflect greater self-efficacy. This instrument has demonstrated strong reliability and validity and has been widely validated in various clinical populations. The Spanish version demonstrates high internal consistency and test–retest reliability, with a Cronbach’s alpha coefficient ranging from 0.88 to 0.95 [53]. Patient adherence [54] and satisfaction with the intervention will also be assessed. To this end, an adherence diary will be used [55], along with a satisfaction questionnaire [56].

In addition to adherence and satisfaction, feasibility will be assessed to evaluate the practicality of implementing the telematic home-based programme. Feasibility outcomes will include: (1) the number and type of technical issues encountered during supervised online sessions; (2) the proportion of successfully completed telematic sessions; (3) participant-reported ease of use and accessibility of the video-conferencing platform; and (4) a brief self-reported questionnaire evaluating participants’ baseline digital literacy and access to compatible devices (smartphone, tablet, or computer). These data will be analyzed descriptively and will provide valuable information on the acceptability and technical viability of telematic interventions in patients with permanent colostomies.

#### 2.7.2. Covariables

Anthropometric data such as age, gender, and body mass index, and clinical data such as personal medical history, indication for surgery, regular medication use and comorbidities assessed with the Charlson Comorbidity Index will be recorded [37].

### 2.8. Sample Size Calculation

An a priori sample size calculation was based on the minimum clinically important difference (MCID) of the physical activity level interference estimated to be 1100 daily steps [57]. Using G*Power version 3.1.9.2, we obtained a sample size of 44 participants, equally distributed between the treatment and control groups, based on a confidence level of 95% (α = 0.05) and a power of 80% (β = 0.2). Anticipating a 15% dropout rate, the total sample size was increased to ensure adequate statistical power, resulting in a sample size of 51 participants.

